**Method:**

The study is a multi-centre, prospective, case-control, observational study. The study will include 100 neonates (50 subjects and 50 controls). Echocardiography and cerebral and abdominal ultrasound will be performed in the first 1/2 days after birth as well as during warming i.e., on day 4/7 of life. In neonatal controls these examinations will be performed for indications other than hypothermia, most frequently because of poor adaptation.

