### Study population

3.3.

The study will include 100 neonates (50 subjects and 50 controls).
•Neonates with gestational age ≥35, who experienced an episode of perinatal ischaemia and who were qualified for hypothermia treatment according to the Standards of Medical care of Neonates in Poland will be enrolled to the subject group (T) (Table 5)•Healthy, term neonates, who underwent echocardiography on days 3–7 of life (after closure of ductus arteriosus, or with trace, insignificant haemodynamic ductus arteriosus) for reasons such as difficult adaptation, gestational diabetes of the mother etc.

**Table 5 T5:** Indications for hypothermic treatment according to the standards of medical care of neonates in Poland 2021 (3).

Indications for TH		
Criteria Group A. Neonates born at ≥35 weeks of gestation, who experienced a period of hypoxia and at at least one of the factors in each of the sub-groups		Group B-neurological criteria. Neonates fullfilling the criteria of group with A with fluctuating states of consciousness who has at least one of the following factors:
Sub-group 1	Sub-group 2	– Hypotonia – Abnormal response to stimuli, including abnormal occulomoor or pupillary reflexes – Absent or weak sucking reflex – Clinically confirmed convulsions
– Apgar score ≤5 week 1, 3, 5, 10 min after birth – Continuous resuscitation with tracheal or mask withinn 10 min after birth	– Cord blood or blood pH within 1 h of life ≤7, however, with specicif assesment of pH results in the region of 7.01–7.15 – A BE base deficiency of at least 16 mmol/l cord blood or other samoles samples within 60 min after birth.	

Enrolment of patients will be based on patient medical records. Physicians responsible for recruitment of patients will gather additional information associated with the inclusion and exclusion criteria (Table 6) through detailed history, taking into account the clinical condition of patients and the results of tests. The study procedure will be explained to patient's guardians who will also receive an information leaflet. Guardians will then be asked to provide two copies of informed consent. Consent forms and information papers will be provided solely in the Polish language.

**Table 6 T6:** Inclusion and exclusion criteria.

Inclusion criteria (subjects)	Exclusion criteria

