### Strengths of the study

3.6.

To assess the hemodynamics of the circulatory system, the authors also used echocardiographic measurements, the value of which is independent of the presence of DA, PFO, HR, age, body weight, such as the TEI index for RV and LV, and used the tissue Doppler function to assess the myocardium.

An additional advantage of the study is the large size of the study group compared to other publications.

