## Study outcomes

5.

5.1.

•Assessment of the influence of TH on systolic-diastolic functions of the left and right ventricles in comparison with the control group•Assessment of the effect of the warming phase on the systolic-diastolic functions of the left and right ventricles in comparison with the control group

5.2.

•Assessment of the influence of TH on the cerebral, visceral and renal circulation in comparison with the control group•Assessment of the effect of the warming phase on the cerebral, visceral and renal circulation in comparison with the control group

This study assesses the hemodynamic changes by means of echocardiographic Doppler examination in neonates with HIE during TH in the warming phase in comparison with the control group of healthy neonates.

The intention is to assess the impact of TH on the cardiovascular system, including the cerebral, visceral and renal circulation.

TH may have an adverse effect on the cerebral circulation by increasing vascular resistance and loss of adaptation of the cerebral vessels, which in turn can lead to hypoperfusion of vital organs.

The effect of the warming phase on the cardiovascular system by increasing heart rate and improving cardiac output will also be carefully examined. The assumption is that the changes in blood pressure (systolic/diastolic) have a decisive impact on the metabolism of drugs, including vasopressors/inotropics, which in turn affects their choice and fluid therapy.

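### Cooled infants may enter from 35 weeks but controls must be term, so the comparisons with controls are open to confounding by gestational age

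*Protocol article*

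**What the plan says.** Section 3.3 (Study population) fixes two groups: "The study will include 100 neonates (50 subjects and 50 controls").

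- Cooled group (T): "Neonates with gestational age ≥35, who experienced an episode of perinatal ischaemia" and who qualified for hypothermia. Tables 2 and 6 repeat the 35-week floor.
- Control group (N): "Healthy, term neonates, who underwent echocardiography on days 3–7 of life", with the duct closed or haemodynamically insignificant, and scanned "for reasons such as difficult adaptation, gestational diabetes of the mother etc".

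The Method part of the abstract says of the control scans that they are done "most frequently because of poor adaptation". The text under Table 4 in section 3.1 says much the same. Section 5 (Study outcomes) nevertheless describes the comparison as being "in comparison with the control group of healthy neonates".

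Section 5 defines every primary and secondary outcome as T compared with N. No matching and no common gestational-age range appears anywhere in the article. Gestational age and birth weight are both on the data list in section 7. The reason for a control's scan is not.

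**The concern.** The study is not randomised, so a T–N difference can be read as a haemodynamic finding only if the groups are otherwise comparable. The eligibility rules themselves build in one difference. An infant of 35 or 36 weeks can be a subject but never a control. If a measure changes with maturity, part of the T–N difference for that measure reflects gestational age.

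A later analysis plan cannot fully repair this. With no late-preterm infants in N, a model adjusted for gestational age has to extrapolate from term controls to the late-preterm subjects.

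A second, smaller matter is the reference group's description. Controls are called healthy but are selected because a clinician had a reason to scan them. A reader of the results would not know whether N is a normal reference or a clinically selected one.

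**Working it through.** **The plan's own figure.** The total of 100 cannot be reproduced. Section 9 gives the non-central F formula but no alpha, power, effect size or SD. A yardstick therefore needs assumptions: two-sided alpha 0.05 and 80% power.

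- Exact F test, k = 2, N = 100: Cohen's f = 0.283, so the detectable difference is d = 2 × 0.283 = 0.566, about 0.57 SD.
- Normal approximation: (1.96 + 0.84) × √(2/50) = 2.80 × 0.20 = 0.56 SD.

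**Possible shift from unequal gestational-age ranges.** Take term as 37 weeks or more (the article does not define it), and suppose that the term infants in T have the same maturity as N. Then

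shift (SD) = share of T born at 35–36 weeks × late-preterm versus term difference (SD).

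Neither input is in the documents. I take shares of 10–30% and differences of 0.3–1.0 SD. The standard error of T–N is √(2/50) = 0.20 SD. The second figure in each cell is the chance that a nominal 5% two-sided test rejects when nothing but maturity differs.

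| Share of T at 35–36 weeks | 0.3 SD | 0.5 SD | 1.0 SD |
|---|---|---|---|
| 10% | 0.03; 0.053 | 0.05; 0.057 | 0.10; 0.079 |
| 20% | 0.06; 0.060 | 0.10; 0.079 | 0.20; 0.170 |
| 30% | 0.09; 0.073 | 0.15; 0.117 | 0.30; 0.323 |

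The shift runs from 0.03 to 0.30 SD, that is 0.03/0.566 = 5% to 0.30/0.566 = 53% of the detectable difference.

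**Cross-check by weeks.** Assume means of 36 weeks for late-preterm and 39.5 for term infants, a gap of 3.5 weeks. Shares of 10–30% give a mean T–N gap of 0.35–1.05 weeks. At an assumed 0.1–0.2 SD per week the shift is 0.35 × 0.1 = 0.035 to 1.05 × 0.2 = 0.21 SD, inside the range above.

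**Which measures are exposed.** Among the ventricular measures grouped in section 3.5:

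- LVO is expressed per kg (section 3.4.2A). SVC flow, listed there as systemic flow, is also per kg (3.4.3A).
- FS, E:A, E′:A′ and MPI are ratios.
- The authors state that the Tei index does not depend on age or body weight (section 3.6).
- S′, TAPSE and MAPSE are neither indexed nor ratios.

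Outside the heart, RI is also a ratio. Indexing and ratios deal with body size. They do not prove independence from maturity, but the documents give nothing to show dependence either.

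**The case against.** The case against is substantial, and parts of it stand.

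- **Analysis model.** A reader might infer from the one-factor F test in section 9 that the comparison will be unadjusted. The section does not support that. It explains a power calculation and states no analysis model for T–N. The analysis plan is not shown, and a covariate list is commonly left to it. This stands, so the point rests on eligibility and not on missing covariates.
- **Age dependence of the other measures.** A reader might infer from section 3.6, which praises measures "the value of which is independent of the presence of DA, PFO, HR, age, body weight, such as the TEI index", that all the others depend on age and weight. That does not follow. The index is offered as an example, and nothing is said about the rest.
- **Size.** Per-kg flows, ratios and the exclusion of infants small for gestational age limit confounding by body size. This largely stands, although the tables do not say whether that exclusion covers controls.
- **Reach.** The comparison of T1 with T2 within infants does not involve controls, and section 2.1 does not mention them. This stands, but section 5 still frames every outcome against N.
- **The label.** Controls are scanned on days 3–7 with no significant duct, and maternal gestational diabetes does not itself make the infant ill. So 'healthy' is partly qualified, but poor adaptation as the most frequent indication still sits badly with it.

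The different gestational-age ranges and the lack of late-preterm controls are untouched by any of this.

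**Conclusion.** The point holds as a risk of confounding created by the eligibility rules. It would go too far to say that the T–N contrasts *are* biased by maturity and size. The documents give neither the share of T born at 35–36 weeks nor any effect of maturity, and the direction may differ from one measure to another. The 0.03–0.30 SD range is an illustration under stated assumptions, to be set against about 0.57 SD detectable. At its low end the effect is negligible (rejection rate 0.053). At its high end it would matter (0.323). S′, TAPSE and MAPSE are the measures mainly exposed.

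The control label is a matter of wording to reconcile. Selection by scan indication could move T–N in either direction, and its size cannot be derived.

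Removing the gestational-age difference would not isolate hypothermia. T infants also differ from N by the asphyxia itself, and no adjustment for maturity separates the two.

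**What to change.** 1. Use the same gestational-age range in both groups for every T–N contrast. Either admit controls from 35 weeks or, if control enrolment is finished, run or repeat these contrasts in infants of 37 weeks or more. State the cut-off for term.
2. Adjust these contrasts for gestational age and birth weight. Both are already collected under section 7.
3. Reconcile the word 'healthy' in sections 3.3 and 5 with the indications given in the abstract and in sections 3.1 and 3.3.
4. Record each control's scan indication and use it only in a sensitivity analysis. Poor adaptation and maternal diabetes are the only two indications named, and the first is the most frequent. Dropping both from the main analysis could remove most of N.

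**Cost.** A change of wording, two covariates already on file and one extra data field. Restricting to 37 weeks or more loses the late-preterm T infants: 5 to 15 of 50 at the assumed shares. The standard error then rises from 0.200 to √(1/45 + 1/50) = 0.205 or √(1/35 + 1/50) = 0.220 SD, before any gain from the covariates. Admitting controls from 35 weeks avoids that loss, but brings in late-preterm infants scanned for clinical reasons, which is a further reason to record the indication.

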### Echocardiographic examination

3.4.

All cardiac scans will be performed in standard echocardiographic projections with the aid of a sector probe with high frequency 8–12 MHz on a Philips camera. Echocardiography will be performed with continuous electrocardiography (ECG) recording from an ultrasound apparatus. Heart rate (HR) will be recorded. Doppler examination of the cerebral, renal and visceral circulation is an essential examination to assess haemodynamics and is routinely performed in ill neonates.

The scans will be saved as video recordings on storage media. In order to decrease the duration of patient examination to a minimum of 10–15 min, echocardiographic measurements will be performed on the recorded film clips or in the Image Arena echocardiographic program.

All parameters will be measured during end expiration and three consecutive cardiac cycles will be measured and averaged for each measurement.

LV and RV systolic and diastolic function on cardiac echocardiography will be assessed using the following imaging options (11–13):

3.4.A.

Pulse Doppler, M-mode, Tissue Doppler (TDI) (14). The examined parameters will also be determined by the tissue efficiency index, the so-called Tei-MPI index-Myocardial Performance Index, (in pulse and tissue Doppler option, cardiac output (left ventricular output) CO (LVOT), mitral valve (MV) early diastolic velocity/late diastolic velocity (*E*/*A*) ratio. MV *E*′/*A*′ ratio, SVC (CO), peak systolic velocity (*S*′), *E*′, *A*′, tricuspid valve (TV) early diastolic velocity/late diastolic velocity (*E*/*A*) ratio. TV *E*′/*A*′ ratio, tricuspidal annular plane systolic excursion (TAPSE), mitral annular plane systolic excursion (MAPSE), ductus arterious (DA) evaluation, tricuspidal valve regurgitation (rTV):

3.4.1A.

Two-dimensional (2D) M-mode measurements will be obtained from a parasternal long-axis view. The following measurements will be assessed: aortic diameter (AO) at the level of the valvular annulus, LV internal diameter at end diastole (LVIDd) and at end systole (LVIDs), left atrial size, RV diameter at end diastole (RVDd), and LV posterior wall thickness at end systole (LVPWs) and at end diastole (LVPWd). Fractional shortening (FS) will be calculated (LVIDd − LVIDs)/LVIDd × 100. The ECG will be recorded continuously during the examination.

3.4.2A.

Left ventricular cardiac output will be recorded from an apical 5-chamber view with a pulsed-wave (PW) Doppler with the flow volume measured in the middle of the outflow tract at the level of the ascending aorta. Aortic area will be measured in 2D echocardiography from a parasternal long-axis view. CO_LVOT_ (ml/kg/min) = velocity time integral (VTI) × aortic area × heart rate, The ECG will be recorded continuously during the examination.

3.4.3A.

Superior Vena Cava cardiac input will be recorded from subcostal coronal midsection views with a PW-Doppler with the flow volume measured in the middle of the inflow tract. SVC area will be measured in 2D echocardiography from suprasternal views. CO_svc_ (ml/kg/min) = velocity time integral (VTI) × svc area × heart rate, The ECG will be recorded continuously during the examination.

3.4.4A.

A mitral inflow velocity pattern and tricuspid inflow velocity pattern will be recorded from an apical 4-chamber view with a PW Doppler sample volume positioned at the tips of the mitral leaflets and tricuspid leaflets, respectively. Tricuspid and mitral insufficiencies will be evaluated from the measurement of the spatial distribution of the tricuspid or mitral regurgitation jet using colour Doppler examination in the apical four-chamber view. Mitral incompetence and tricuspid incompetence will be graded as trivial, mild, moderate, and severe.

3.4.5A.

The AcT/RVET ratio will be measured at the parasternal short axis view with a pulsed-wave Doppler sample volume positioned at the tips of pulmonary valve: AcT-acceleration time (time to peak velocity of pulmonary blood flow), and RVET-right ventricular ejection time.

3.4.6A.

PW DTI will be performed using a special software package available on the Philips apparatus. This method is capable of providing measurements of ventricular wall motion velocity by positioning the sample volume at mitral and tricuspid valve annuli. In the apical 4-chambers view, the pulsed Doppler sample volume will be placed at the lateral margin of the mitral annulus and lateral margin of the tricuspid annulus. The systolic velocity (*S*), the early diastolic myocardial velocity (*E*), the late diastolic myocardial velocity (*A*) at the time of atrial contraction, and the ratio of *E*/*A* will be determined. DTI time intervals will be measured from recordings. The intervals (*a*) between the end of the late diastolic annular velocity and the onset of the early diastolic annular velocity will be equal to the sum of the isovolumetric contraction time (ICT), isovolumetric relaxation time (IRT), and ejection time (ET). The ET (*b*) will be measured as the duration of the systolic annular velocity (*S*). The sum of the ICT and IRT will be obtained by subtracting b from a. Then the LV MPI and RV MPI indexes will be calculated as (*a* − *b*)/*b*. The IRT will be measured from the pulsed-wave Doppler tissue recordings as the time interval from the end of the systolic annular velocity to the onset of the early diastolic annular velocity and the ICT will be obtained by subtracting the IRT from (*a* − *b*). The ECG will be recorded continuously during the examination.

3.4.7A.

Pulsed Doppler myocardial perfusion imaging (MPI) for the right ventricle. The tricuspid inflow velocity pattern will be measured from an apical 4-chamber view with a pulsed-wave Doppler sample volume positioned at the tips of the tricuspid leaflets. All parameters will be measured during end expiration and five consecutive cardiac cycles will be measured and averaged for each measurement. Diastolic flow through the tricuspid valve in the apical four-chamber view, including early diastolic (*E*) and late diastolic, i.e., atrial (*A*) waves in m/s, will be measured with calculation of the tricuspid valve *E*:*A* ratio.

RV ET will be measured separately from the parasternal short-axis scan plane with a PW Doppler signal placed at the pulmonary valve annulus in the RV outflow tract. The ECG will be recorded continuously during the examination. The calculation of the Tei index (RVMPI) will be considered meaningful for the RV if the difference in heart rate for the inflow and outflow path is 5 beats/min. The isovolumetric contraction time (ICT), isovolumetric relaxation time (IRT), and ejection time (ET) will be measured, and the MPI calculated using the formula (ICT + IRT)/ET, and calculated as (*a *−* b*)*b*. Doppler echo (clicks) of the opening and closing of the aorta valve (AV) and MV will be used as reference points to estimate the timing of the ejection period.

3.4.8A.

Pulsed Doppler MPI for the left ventricle. The mitral inflow velocity pattern will be recorded from an apical 5-chamber view with a pulsed-wave Doppler sample volume placed below the mitral valve towards the ventricular septum with the PW-Doppler tracing including both the *E*/*A* (positive) and the aortic (negative) blood flow waveforms. Diastolic flow through the mitral valve in the apical five-chamber view, including early diastolic (*E*) and late diastolic, i.e., atrial (*A*) waves in m/s, will be measured with calculation of the valve *E*:*A* ratio. The ECG will be recorded continuously during the examination. The isovolumetric contraction time (ICT), isovolumetric relaxation time (IRT), and ejection time (ET) will be measured, and the MPI will be calculated using the formula: (ICT + IRT)/ET, and calculated as *a* − *b*/*b*.

3.4.B.

Doppler measurements of other organs: resistive index (RI) in RRA, SMA, ACA, MCA (11).

The resistance index has an inverse relationship with blood flow and will be calculated = (PSV − EDV)/PSV. PSV, peak systolic velocity; EDV, end-diastolic velocity. Since bradycardia can interfere with the measurement of blood flow indices: RI and PI, the authors additionally investigated half peak systolic velocity (h-PSV) deceleration time (DT) in ms, which evaluates the time that it takes a single flow velocity waveforms (FVWs) to halve its maximum systolic velocity. A perpendicular line was then drawn from the point of half the maximum velocity to the spectral waveform, which measures the deceleration time in ms (15) Figure 2.

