### Study design

3.1.

This is a multicentre, prospective, case-control, observational study. The number of subjects under observation will be 100 neonates (study summery Tables 2, 3). The enrolment, intervention and assessment schedule is presented in Table 4. Initial echocardiography and cerebral and abdominal ultrasonography will be conducted according to physician recommendation on day 1/2 after birth—hypothermia group echo1 (T1) with repeat examination on conclusion of hypothermia, during warming i.e., on day 4/7 of life—hypothermia group echo2 (T2). In view of the need for cooling of the neonate from the first hour of life there is no possibility to conduct theses examinations prior to introducing hypothermia.

**Table 2 T2:** Study summary.

Title	Echocardiographic and Ultrasound Evaluation of Haemodynamic Parameters in Hypoxic Neonates Treated With Hypothermia.	
Methodology	Multi-centre, prospective, case-control, observational study.	
Study duration	The study will take place from June 2021—June 2023	
Study Centre(s)	Neonatal Clinic and Neonatal Intensive Care unit, Warsaw Medical University [name]	
	ŻELAZNA Medical Center Ltd St. Sophia's Specialist Hospital Medical Centre Department of Prematurity and Neonatal Pathology	
Objectives	**Primary objectives**:	
	Assessment of contraction-relaxation function of the left and right ventricle during therapeutic hypothermia and warming period.	

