**Limitations**
• Cardiovascular haemodynamics during TH may also be disturbed by the administration of inotropic, anticonvulsant sedative agents as well as mechanical ventilation or thrombotic changes.
• The specificity of the transient circulation (presence of patent ductus arteriosus, patent foramen ovale) may interfere with some echocardiographic measurements, such as CO (Cardiac output) for LV (left ventricle) and RV (right ventricle).

**Table 4 T4:** Proposed schedule of enrolment.

Study plan	Birth	1–2 days	3–7 days	0–30 days*
Anthropometry	X			
Medical history collection	X			X
Enrolment	X			
Eligibility assessment		X		
Medication (inotropics, sedatives, anticonvulsants)				X
Ultrasound of brain				X
MRI brain				X
Echocardiography		X^1^	X^2^	

X^1^–1 echo for group T (T1), X^2^–2 echo for group T (T2) and echo in group *N* (*N*).

* Entire observation period.

Images and clips from examinations conducted for indications, other than hypothermia, most frequently because of difficult adaptation, will be used for neonates in the control group (*N*). The study will take place in the period June 2021–June 2023. The proposed protocol of the study is shown in Figure 1.

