#### RRA

3.4.4B.

A transducer with a lower frequency of 5–8 MHz was used. The transducer will be placed on the flank a few centimetres above the level of the umbilicus, the probe marker directed superiorly. The kidney will be identified in the long axis on 2D imaging. Blood flow from the aorta to the renal hilum will be found using Colour Doppler and the PW Doppler cursor will be placed in the RA prior to the point in which it branches in the renal hilum, sliding and tilting the probe to decrease the angle of insonation and to obtain the velocity profile.

In order to assess the repeatability of the measurements, a pairwise comparison will be made between the results of 2 series of measurements performed by one researcher ([name]) (intra-observer variability) and two researchers ([name] and [name]) (interobserver variability). On the basis of these series of measurements, the value of the Pearson linear correlation coefficient (*R*) will be determined—as an indirect measure of the impact of random variability on the measurement results and the coefficient of variation (*V*) defined as the quotient of the mean of the squared differences between the pairs of measurements to the product of the standard deviations of both series of measurements. This method of calculating the coefficient of variation provides for taking into account the systematic error component.

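### Echocardiographic values are read offline from stored clips, and the stated procedure does not mask the reader to group or phase, or the repeat series to the first reading

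*Protocol article*

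**What the plan says.** Section 3.4 separates image acquisition from measurement. "The scans will be saved as video recordings on storage media", and, to keep the bedside examination short, "echocardiographic measurements will be performed on the recorded film clips or in the Image Arena echocardiographic program". The same section then fixes views, sample-volume positions, measurement at end expiration, and averaging over three consecutive cycles (five for right-ventricular pulsed-Doppler MPI, section 3.4.7A).

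Control readings come from separate clinical scans. On this group, the text below Table 4 says: "Images and clips from examinations conducted for indications, other than hypothermia, most frequently because of difficult adaptation, will be used". Cooled neonates are scanned on day 1/2 (T1), "with repeat examination on conclusion of hypothermia, during warming i.e., on day 4/7 of life" (T2). Controls (N) are scanned on days 3–7 with a closed or haemodynamically insignificant duct (section 3.3).

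The ventricular outcomes in section 5 rest on these readings, for example "Assessment of the effect of the warming phase on the systolic-diastolic functions of the left and right ventricles in comparison with the control group".

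For repeatability, the last paragraph of section 3.4.4B says that "a pairwise comparison will be made between the results of 2 series of measurements performed by one researcher", and also by two researchers. These are summarised by "the value of the Pearson linear correlation coefficient" and a coefficient V, the mean squared pair difference divided by the product of the two standard deviations.

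Section 8 gives participating researchers logins to the study information. The only people kept from data are the statistical team, for confidentiality.

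**The concern.** The ventricular measurements depend on the operator. Interval marks define MPI, diameters define fractional shortening, velocity traces and vessel areas define output, and regurgitation gets a four-level visual grade. The study is not randomised, and control clips come from examinations done for other reasons, so their origin identifies the group unless they are coded. A reader who knows the group or phase may place marks, or choose a run of beats, in line with what is expected. Enlarging the sample does not remove such a shift.

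Reading from stored clips is the step at which masking is feasible. The article describes that step in detail and includes a dedicated repeatability check, so reader masking would naturally stand there. It is a matter of measurement design, not something normally left to an analysis plan. Table 3 does not list unmasked reading among the limitations either.

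**Working it through.** **1. Does any section mask the reader?**
- Sections 3.4 to 3.4.4B (acquisition, measurement, repeatability): no coding, removal of identifiers or random reading order.
- Section 3.1 and the text below Table 4 (source of clips): none.
- Section 8: a restriction on the statistical team only.
- Table 3, limitations: the topic is absent.

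**2. What would a reader shift do?** There is no stated figure to reproduce. Section 9 gives an F-test power formula without a significance level, effect size or SD, so only the group sizes (50 and 50, section 3.3) are taken from the article. Assumptions: two-sided α = 0.05, true difference zero, and a systematic shift of b SD in one group's readings.

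The t statistic is then noncentral t with 50 + 50 − 2 = 98 degrees of freedom and noncentrality b × √(50/2) = 5b. The rejection probability is P(t > c) + P(t < −c), where c is the 97.5% point of the central t.

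| Assumed shift b (SD) | Noncentrality | False-positive rate |
|---|---|---|
| 0 | 0 | 5.0% |
| 0.1 | 0.5 | 7.9% |
| 0.2 | 1.0 | 16.8% |
| 0.3 | 1.5 | 31.8% |

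For scale, 50 v 50 has 80% power at this α for a true difference of about 0.57 SD. A shift of 0.2 to 0.3 SD is therefore about a third to a half of that (0.2/0.57 = 0.35; 0.3/0.57 = 0.53).

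**3. Would the repeatability check show it?** Write two readings of one clip as x + b·g + e₁ and x + b·g + e₂, where g marks the group. The difference is e₁ − e₂, so a shift shared by both readings cancels. With true values of SD 1, assumed random error 0.3 SD per reading and two groups of 50:
- No shift: R = 1/(1 + 0.09) = 0.917.
- Shared shift of 0.3 SD: it adds 0.3² × ¼ = 0.0225 to the between-clip variance, so R = 1.0225/1.1125 = 0.919.
- Simulation (4,000 runs, 100 clips) gave R of 0.917 and 0.919, and V of 0.168 without and 0.165 with the shift.

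Both statistics look marginally better when the shared bias is present.

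**4. Where could masking work?**
- T2 v N: scan days overlap (day 4/7 and days 3–7), so coding can hide most cues.
- T1 v N: the T1 scan is early, cooling slows the heart, the ECG is recorded with the images, and ductal findings differ because controls are selected for a closed or insignificant duct. Masking would be partial.

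**The case against.** The strongest reply is that silence is not evidence of unmasked reading. The article condenses a fuller protocol, section 3.2 is not in the text at hand, and nothing says that readers know the group. That stands. A reader might infer that all values are read unmasked; the documents support only that no masking is stated. Likewise, the article does not say that the first series is visible during the second, so inflated repeatability cannot be claimed as fact.

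Several narrower points also stand:
- Offline measurement is explicit for echocardiographic values only; for the organ Doppler indices it is at most implied. The main readers are not identified, only those in the repeatability series.
- The choice of beats is already constrained by end expiration and consecutive cycles, though caliper placement is not.
- A reader might infer a certain bias in one direction, with cooling read as harmful and warming as beneficial. The text is more mixed: section 1.3 allows mean pressure to fall or stay unchanged on warming, section 1.2 notes that trials found no increased risk of pulmonary hypertension, and section 14 asks whether the changes are adaptive.
- Much operator choice occurs at acquisition (view, sample position, angle), beyond the reach of masked reading.
- Heart rate enters cardiac output and the right-ventricular MPI validity check, so it cannot be wholly hidden.

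None of this removes the point. The plan describes the reading step closely, and carrying it out as written leaves the readings unprotected.

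**Conclusion.** The concern holds in limited form. As stated, the procedure measures echocardiographic values offline without masking the reader to group or phase, or the repeat series to the first reading. The operator-placed comparisons with controls are therefore open to expectation bias that the planned R and V would not detect if both readings share it.

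The size and direction of any bias are unknown. The 7.9%, 16.8% and 31.8% rest on assumed shifts of 0.1, 0.2 and 0.3 SD, a two-sided 5% t-test and 50 v 50; they show sensitivity and are not estimates for this study. This is a cheap improvement to the measurement procedure. It does not show that results would be wrong.

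**What to change.** Add to section 3.4:
- Stored clips are exported under a study code without name, date, group or temperature, mixed across T1, T2 and N, and read in random order by the existing researchers.
- The second intra-observer series is read without access to the first.
- The same applies to organ Doppler wherever it is measured from stored images.

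Add to the limitations in Table 3 that masking of T1 is incomplete because of heart rate, ECG and ductal findings, and that masked reading does not remove bias at image acquisition. If readings have already been made, either re-read the stored clips under code or, if they were unmasked, say so as a limitation.

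The cost is coding and shuffling about 50 × 2 + 50 = 150 examinations. The article gives no figure for the effort, but the clips are already stored and no extra patients or scans are needed. The sample size does not change.
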